**Expedited and periodic safety update reporting by BMS:**

It is the Sponsor-Investigator’s responsibility to report events to their Local HA. In addition, suspected serious adverse reactions (whether expected or unexpected) shall be reported by BMS to the relevant competent health authorities in all concerned countries according to local regulations (either as expedited and/or in aggregate reports).

In accordance with local regulations, BMS will notify Sponsor-Investigator of all reported SAEs that are suspected (related to the investigational product) and unexpected (ie, not previously described in the IB). An event meeting these criteria is termed a **Suspected, Unexpected Serious Adverse Reaction (SUSAR)**. Sponsor-Investigator notification of these events will be in the form of either a SUSAR Report or a Semi-Annual SUSAR Report. Sponsor-Investigator (or delegate) will receive these reports through the FastTrack portal.

Other important findings which may be reported by BMS as an Expedited Safety Report (ESR) include: increased frequency of a clinically significant expected SAE, an SAE considered associated with study procedures that could modify the conduct of the study, lack of efficacy that poses significant hazard to study subjects, clinically significant safety finding from a nonclinical (eg, animal) study, important safety recommendations from a study data monitoring committee, or Sponsor-Investigator or BMS decision to end or temporarily halt a clinical study for safety reasons.

Upon receiving an ESR from BMS, the Sponsor-Investigator **must review and retain the ESR with the IB**. Where required by local regulations or when there is a central IRB/IEC for the study, the Sponsor-Investigator will submit the ESR to the appropriate IRB/IEC. The investigator and IRB/IEC will determine if the informed consent requires revision. The investigator should also comply with the IRB/IEC procedures for reporting any other safety information.

NON-SERIOUS ADVERSE EVENT COLLECTION AND REPORTING

The collection of non-serious AE information should begin following the subject’s written consent to participate in the study. All non‑serious adverse events (not only those deemed to be treatment-related) should be collected continuously during the treatment period and for a minimum of 100 days following the last dose of study treatment.

Non-serious AEs should be followed to resolution or stabilization, or reported as SAEs if they become serious. Follow-up is also required for non-serious AEs that cause interruption or discontinuation of study drug and for those present at the end of study treatment as appropriate.

Non-serious Adverse Events (AE) are to be provided to BMS in aggregate via interim or final study reports as specified in the agreement or, if a regulatory requirement [eg, IND US trial] as part of an annual reporting requirement.

PREGNANCY

If, following initiation of the investigational product, it is subsequently discovered that a study participant is pregnant or may have been pregnant at the time of investigational product exposure, including during at least 5 half-lives after product administration, the investigational product will be permanently discontinued in an appropriate manner (eg, dose tapering if necessary for participant).

The Sponsor-Investigator must immediately notify [**[contact]**](mailto:[contact]) of this event and complete one of the following forms **within 24 hours of awareness** of the event via either the CIOMS, MedWatch or appropriate Pregnancy Surveillance Form in accordance with **SAE reporting procedures.**

Protocol-required procedures for study discontinuation and follow-up must be performed on the participant.

Follow-up information regarding the course of the pregnancy, including perinatal and neonatal outcome and, where applicable, offspring information must be reported on the **CIOMS, MedWatch, BMS Pregnancy Surveillance Form, or approved site SAE form**. A BMS Pregnancy Surveillance Form may be provided upon request.

Any pregnancy that occurs in a female partner of a male study participant should be reported to BMS. Information on this pregnancy will be collected on the Pregnancy Surveillance Form. In order for Sponsor-Investigator or designee to collect any pregnancy surveillance information from the female partner, the female partner must sign an informed consent form for disclosure of this information.

LABORATORY TEST ABNORMALITIES

All laboratory test results captured as part of the study should be recorded following institutional procedures. Test results that constitute SAEs should be documented and reported to BMS as such.

The following laboratory abnormalities should be documented and reported appropriately:

- any laboratory test result that is clinically significant or meets the definition of an SAE
- any laboratory abnormality that required the participant to have study drug discontinued or interrupted
- any laboratory abnormality that required the subject to receive specific corrective therapy.

It is expected that wherever possible, the clinical rather than laboratory term would be used by the reporting investigator (eg, anemia versus low hemoglobin value).

OTHER SAFETY CONSIDERATIONS

Any significant worsening noted during interim or final physical examinations, electrocardiograms, X-rays, and any other potential safety assessments, whether or not these procedures are required by the protocol, should also be recorded as a non-serious or serious AE, as appropriate, and reported accordingly.

ADVERSE EVENT REPORTING FOR SPECIFI SITUATIONS (remove if not applicable):

- **Immune-Mediated AEs (Product Specific, Usually a regulatory requirement)**

Immune-Mediated AEs are required in **ISR Protocols with Registrational Intent**.

Every AE must be assessed by the investigator with regard to whether it is considered immune-mediated. For events which are potentially immune-mediated, additional information must be collected.

Immune-mediated adverse events (IMAEs) are AEs consistent with an immune-mediated mechanism or immune-mediated component for which non-inflammatory etiologies (eg, infection or tumor progression) have been ruled out. IMAEs can include events with an alternate etiology which were exacerbated by the induction of autoimmunity. Information supporting the assessment will be collected.

- **AEs of Special Interest (Product Specific. Usually a regulatory requirement)**

ADVERSE EVENT RECONCILIATION PROCESS

The Sponsor-Investigator (or designee) will reconcile the clinical database AE cases (case level only) transmitted to BMS Global Pharmacovigilance ([[contact]](mailto:[contact])).

- The Sponsor-Investigator will request the SAE reconciliation report (and include the BMS protocol number) from BMS GPV&E ([[contact]](mailto:[contact])) every 3 months and prior to data base lock or final data summary
- GPV&E will send the Sponsor-Investigator the report to verify and confirm all AE and SAEs have been transmitted to BMS GPV&E.
- The data elements listed on the GPV&E reconciliation report will be used for case identification purposes. If the Sponsor-Investigator determines a case was not transmitted to BMS GPV&E, the case should be sent immediately to BMS ([[contact]](mailto:[contact])).

PRODUCT QUALITY COMPLAINTS (PQCs)

**Definition**

Any communication about a **BMS Product** that alleges deficiencies related to identity, quality, durability, reliability, safety, effectiveness, performance, tampering, diversion, and/or counterfeiting/falsification of a drug, combination product, or device after it is released for distribution to market or clinic by either: (1) BMS or (2) distributors or partners for whom BMS manufactures the material. This includes all components co-packaged with the drug, such as drug containers, delivery system, labelling, and inserts.

**BMS product:** Commercial or investigational materials (i.e., drugs, devices, biologics or any combination thereof) and their packaging components, whether they are produced or distributed by BMS or by third parties under contract with BMS, and products that are being manufactured for BMS by third parties.

**Reporting**

Product Quality Complaints must be reported to BMS **within one (1) business day** of awareness to [**[contact]**](mailto:[contact])**.**

In the event of a suspected product quality issue, the affected product must be quarantined immediately at the Investigational site.

The affected product should not be disposed unless retention presents a risk to personnel (e.g., cytotoxic, risk of injury from broken glass or sharps).

When reporting, as much product information as possible should be reported. At a minimum, but not limited to, include:

- ISR Study number, site reference, product description, impacted batch number, container number(s), photographs, and any other supporting information

# Study Management

## Ethical guidelines and informed consent form

This clinical trial must comply with the Declaration of Helsinki (1996 Edition), Good Clinical Practice (GCP) promulgated by the National Medical Products Administration (NMPA), and relevant regulations. The trial must be approved by the ethics committee prior to the start; Any amendment to the protocol during the trial should be reported to the Ethics Committee and approved.

The clinical investigators will follow all applicable rules and regulations to protect subjects. The informed consent form used during the informed consent process must be approved by the ethics review board and available for inspection.

The clinical investigator must inform the subject that participation in the clinical trial is voluntary, that the subject has the right to withdraw from the trial at any stage of the trial at any time without discrimination or retaliation, and that his/her medical treatment and rights and interests are not affected, and that he/she can continue to receive other forms of treatment. The subjects must be informed that their personal data in the trial will be kept confidential. The subjects shall also be informed of the nature of clinical trial, trial objective, expected possible benefits and possible risks and inconveniences, other alternative treatment options and the rights and obligations of the subjects conforming to the provisions of Declaration of Helsinki, so as to give the subjects sufficient time to consider whether they are willing to participate in the trial and sign the informed consent form.

Prior to performing any protocol-required procedures, the subjects must:

- Be informed of the study as well as all contents and terms of the informed consent form.
- Be given adequate time to ask questions and consider participation.
- Voluntary consent to participate in the study.
- Sign and date the IRB/IEC-approved informed consent form.

Any significant changes in the study require a protocol amendment. The investigator should not make any changes to the study without prior IRB/IEC approval unless it is necessary to eliminate an obvious and immediate hazard to the subject. Changes to the protocol to eliminate an apparent immediate hazard to subjects may be implemented immediately, but must be documented in the protocol amendment, reported to the IRB/IEC, and submitted to the appropriate regulatory agencies within the required timeline. All protocol modifications must be subject to the same review and approval process as the original protocol.

The investigator is responsible for submitting the interim report/annual review report regularly according to the relevant requirements of the Ethics Committee, and notifying the Ethics Committee that the trial has ended after the trial is completed

## Protocol amendment

This "Clinical Study Protocol" and "Clinical Study Case Report Form" are developed by the principal investigator and will be implemented after approval by the Ethics Committee of this hospital. During the clinical trial, any amendment to the trial protocol should be consulted by the investigator and approved by the Ethics Committee.

## Quality assurance of clinical trial

In order to ensure the quality of clinical trials, the principal investigator will jointly discuss and develop the clinical study plan before the formal trial is initiated. Protocol training should be performed for all relevant study personnel participating in the clinical trial.

Investigational medicinal products must be managed according to SOPs, including drug supply, storage, dispensing and recovery, and destruction.

According to the GCP guidelines, necessary procedures should be adopted during study design and conduct to ensure the accuracy, consistency, completeness, and authenticity of the data collected. All results and abnormal findings observed in the clinical trial should be timely and seriously verified and recorded to ensure the data integrity. All instruments, equipment, reagents, and standard substances used for various examination items in the clinical trial should have strict specifications and must work in a normal state.

# Statistical analysis of data

## Sample Size

- The primary endpoint is pCR. This study has 80% power to detect an increase in pCR rate from 5% to 20% with a one-sided alpha of 0.05. Considering a 10% drop-out rate, 46 patients will be enrolled.

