| **Exclusion criteria** | Patients with any of the following are not to be enrolled in the study:   1. Multiple types of cancer, or accompanied by tumors other than rectal cancer 2. Having received any anti-cancer treatment (surgery, medication, etc.) within the past 5 years 3. Recent history of major surgery 4. Conditions affecting the absorption of capecitabine through the gastrointestinal tract (such as inability to swallow, nausea, vomiting, chronic diarrhea, etc.) 5. Having any type of uncontrolled, severe, accompanying disease, allergic to any component of the study; estimated survival period≤5 years due to any reason 6. Preparing or previously having undergone organ or bone marrow transplantation 7. Receiving immunosuppressive or systemic hormone therapy within 1 month before inclusion for immunosuppression 8. For patients with a history of central nervous system diseases, the investigator needs to judge whether the clinical severity hinders signing the informed consent or affects the patient's oral medication compliance 9. Other situations/problems that may affect the research results or lead to the termination of the study (such as alcohol abuse, drug abuse, etc.) 10. Pregnant or lactating women, or women planning to conceive during treatment |
| **Statistical considerations** | The primary endpoint is pathological complete response (pCR). The trial is designed as a single-arm Phase II study with 80% power to detect an increase in the pCR rate from 5% (historical control for pMMR/MSS LARC after standard long-course radiotherapy) to 20% with a one-sided alpha of 0.05. Accounting for an anticipated 10% drop-out rate, a total of 30 patients will be enrolled. |
| **Period during which study was conducted** | First patient enrolled: 2023-01-01.  Planned enrollment duration: approximately 24 months to accrue ~30 patients.  Planned follow-up after treatment: 5 years (for disease-free survival and overall survival assessments). |

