# Research design

## Overall Design

This study is a single-arm, open-label, phase II trial to observe and evaluate the efficacy and safety of capecitabine-based long-term radiotherapy followed by 3 cycles Sintilimab (PD-1 inhibitor) for locally advanced rectal cancer.

The study aims at the treatment-naïve patients with gastric or gastroesophageal junction adenocarcinoma at the staging of cT3-4 or N+, M0 (staging according to AJCC version 8).

With pathological complete response rate (pCR) as the primary study endpoint, 46 patients with resectable locally advanced gastric adenocarcinoma and gastroesophageal junction adenocarcinoma who have not received treatment are planned to be enrolled.

Subjects are enrolled after signing informed consent and passing screening.

Subjects will receive the following treatments:

45-50.4Gy/25 fractions + 5-FU long-course radiotherapy and chemotherapy (5 times per week for 5 weeks, total dose of 45 to 50.4Gy) before surgery →PD-1 monoclonal antibody (Sintilimab, 200mg, once a week, for 3 weeks) →radical surgery

The surgery was scheduled 8-12 weeks after radiotherapy completion.

Radiographic assessment:

All lesions are recorded and assessed according to RECIST 1.1. Imaging examinations include chest CT, enhanced CT scans of the abdomen and pelvis, and chest CT plain scan + abdominal and pelvic MRI scans could be performed if allergic to enhanced CT contrast agents; brain enhanced MRI or enhanced CT is also required to rule out brain metastases in patients with suspected brain metastases. Bone scan should be performed when bone metastasis is confirmed or clinically suspected. Colonoscopy examinations should be conducted before the start of radiotherapy, after the completion of radiotherapy, and after immunotherapy to evaluate the therapeutic effects.

Within 1 weeks after the radiotherapy; within 1 weeks after the frist dose of PD-1 monoclonal antibody in Cycle 3; at the end of treatment; and imaging assessments at least every 3 months in subsequent Year 1 and at least every 6 months from Year 2 until radiographic progression or recurrence, receipt of other antineoplastic therapy, withdrawal of informed consent, loss to follow-up, or death.

If treatment is discontinued during the treatment period for reasons other than radiographic progression, imaging should be performed at the end of treatment unless imaging has already been performed within 28 days.

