# Clinical study progress

The estimated enrollment date of the first subject: January 2023

Enrollment duration: 1 year

Follow-up after treatment: 5 years

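### One set of design inputs gives two enrolment totals, 30 and 46; the 46 was not reproduced at 80% power and is tied in the design section to a gastric cancer population

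*Protocol*

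**What the plan says.** Section 9.1 (Sample Size) takes pCR rates of 5% and 20%, a one-sided test at 0.05 and 80% power, and concludes: "Considering a 10% drop-out rate, 46 patients will be enrolled".

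The Protocol Summary, under statistical considerations, gives the same two rates, alpha, power and drop-out, and ends: "Accounting for an anticipated 10% drop-out rate, a total of 30 patients will be enrolled". Its study-period entry repeats the smaller number: "Planned enrollment duration: approximately 24 months to accrue ~30 patients".

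The Overall Design section uses the larger number for a different disease: "46 patients with resectable locally advanced gastric adenocarcinoma and gastroesophageal junction adenocarcinoma who have not received treatment are planned to be enrolled". It describes the target population as "gastric or gastroesophageal junction adenocarcinoma at the staging of cT3-4 or N+, M0". The title, the summary, the opening sentence of Overall Design and both sets of eligibility criteria describe rectal cancer; the criteria specify adenocarcinoma, stage II/III, T4b excluded.

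Section 11 (Clinical study progress) has "Enrollment duration: 1 year", against about 24 months in the summary.

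Section 9.2 (Analysis Population) makes ITT the primary efficacy set. The protocol names no sample-size method and gives no number of pCRs that would count as success.

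**The concern.** Both totals are current text of Version 1.0, so this is not a leftover in an amendment log. Nor can a statistical analysis plan settle it, because the protocol itself fixes the enrolment number and fixes it twice. With one set of inputs and one method, at most one of the totals can be right.

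The size determines when enrolment ends, how many patients the ethics committee agreed to expose, and the smallest number of pCRs compatible with a one-sided 5% test. The rule does not carry over between sizes: at least 4 pCRs is a valid rule for 27 patients, but applied to 46 it has a one-sided error of 0.197. In an open-label single-arm trial, a document that supports two stopping points also makes it hard to show later which one was planned.

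**Working it through.** **Inputs.** p0 = 0.05, p1 = 0.20, one-sided alpha 0.05, power 0.80, drop-out 0.10, identical in Section 9.1 and the Protocol Summary.

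**Formulas.** For n patients and success at c or more pCRs, with X binomial(n, p):
- alpha = P(X ≥ c | p = 0.05) and power = P(X ≥ c | p = 0.20);
- c is the smallest count with alpha ≤ 0.05;
- enrolled = evaluable / (1 − 0.10), rounded up.

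**Step 1: reproduce 30.** At n = 26, c = 4 the power is 0.793, which is too low. At n = 27, c = 4, alpha = 0.0437 and power = 0.8177, so 27 is the smallest n that meets both limits. Then 27/0.9 = 30, the summary's figure.

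**Step 2: try to reproduce 46.** Since 41/0.9 = 45.6, the 46 corresponds to 41 evaluable patients. At one-sided 0.05 and 80% power, other methods give:

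| Method | Evaluable | Enrolled |
|---|---|---|
| Normal approximation, null and alternative variances | 22 | 25 |
| Same, continuity-corrected | 28 | 32 |
| Arcsine | 28 | 32 |
| Normal approximation, variance at p1 only | 44 | 49 |
| Exact, power at least 80% for every larger n | 33 | 37 |
| Simon minimax | 27 | 30 |
| Simon optimal | 29 | 33 |

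None gives 46.

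**Step 3: what each size delivers (exact).**

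| Patients counted | Success at | alpha | Power |
|---|---|---|---|
| 27 evaluable | ≥ 4 | 0.044 | 0.818 |
| all 30, all with outcomes | ≥ 4 | 0.061 (too high) | 0.877 |
| all 30, all with outcomes | ≥ 5 | 0.016 | 0.745 |
| 41 evaluable | ≥ 5 | 0.053 (too high) | 0.934 |
| 41 evaluable | ≥ 6 | 0.016 | 0.856 |
| all 46, all with outcomes | ≥ 6 | 0.026 | 0.920 |

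**Step 4: N = 30 under ITT.** If each patient has a 10% chance of dropping out and drop-outs count as non-responders, the pCR probabilities per enrolled patient become 0.9 × 0.05 = 0.045 and 0.9 × 0.20 = 0.18. With n = 30 and c = 4, alpha is about 0.044 and power about 0.81. So 30 enrolled delivers the stated 80% on 27 evaluable patients, or on all 30 if about 10% drop out and count as failures. It does not if all 30 contribute outcomes.

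**Step 5: size of the discrepancy.** 46 − 30 = 16 patients; 16/30 = 53%.

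**The case against.** The contradiction between the totals is not open to dispute. The case on the other side concerns how far it reaches.

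- **Is 30 the only answer?** No. The protocol names no method, and the same inputs give 25 to 49 enrolled depending on the formula. What stands is narrower: 30 is the exact-binomial answer, and 46 was not reached at 80% power.
- **Is 30 therefore the approved or intended size?** The arithmetic cannot show that. The summary gives 30 twice, and the body gives 46 twice. The sponsor has to say which was intended.
- **Where did the 46 come from?** A reader might infer a 90%-power calculation, a two-stage design or text carried over from a gastric protocol. More than one route leads to 46 (for example, 90% power with a continuity correction gives 41, hence 46), so a numerical match identifies none of them. The protocol describes no two-stage design, and carry-over is plausible but unproven.
- **Do the two sizes explain the missing success threshold?** A reader might infer so. They do not: the protocol states no threshold under either size, and that may properly sit in an analysis plan. The two sizes only mean that no single threshold follows from the protocol.
- **Is the population undefined?** No. The eligibility criteria are consistently rectal. The gastric sentences are an isolated error in the design section, not a competing definition.
- **Will the team choose its stopping point on the results?** That is a risk only; no efficacy looks are described. The accrual mismatch is administrative and adds nothing to the severity.

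**Conclusion.** The point holds in this form and needs correction. One set of inputs is given two enrolment totals, 16 patients apart. The total of 30 follows exactly from those inputs by the exact single-stage binomial method. The total of 46 does not match the stated 80% power: it gives 0.856 on 41 evaluable patients or 0.920 on all 46, both with at least 6 pCRs.

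Moving to 30 does not finish the matter. ITT is the primary set, and if all 30 contribute outcomes the valid rule (at least 5) has power 0.745. The stated 80% at N = 30 therefore depends on which patients form the denominator and how drop-outs are counted.

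These figures assume a single-stage exact test and independent patients; the calculation in which drop-outs count as failures also assumes that drop-out is unrelated to response.

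**What to change.** 1. Give one N in the Protocol Summary, the Overall Design section and Section 9.1. The stated inputs support 30. If 46 is the intended size, replace the 80% with the power that 46 gives under its rule.
2. Next to N, state the sample-size method, the denominator, how patients without a pathological result are counted, and the minimum number of pCRs. For 30 enrolled, specify either at least 4 of 27 evaluable, or a rule for all 30 that says how drop-outs count; at least 4 of 30 exceeds 5% if everyone contributes an outcome.
3. Replace the gastric and gastroesophageal junction sentences in Overall Design with the rectal population in the eligibility criteria.
4. Use one accrual period in the Protocol Summary and Section 11.

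**Cost.** The changes are to wording. The protocol requires ethics approval for amendments, and the summary records a first patient enrolled on 2023-01-01, so an amendment is needed. Choosing 30 adds no patients; choosing 46 means 16 more than the summary plans.
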